**Methods::**

A randomized, controlled, double-blind clinical trial is proposed, which will involve 33 individuals (n = 11 per group) of both sexes, ages 18 to 45 years in 3 groups: LED group; placebo group; and control group, submitted to 6 non-consecutive sessions of photobiomodulation totaling 2 weeks of treatment. The Research Diagnostic Criteria for Temporomandibular Disorders—RDC/TMD will be used to assess and determine the participants’ TMD. The pain will be assessed using the Visual Analog Scale – VAS, the mandibular range of motion will be determined with the aid of a digital caliper, and the electrical activity of the masticatory muscles will be verified by electromyography. A mixed plate of 18 red LEDs—660 nm and 18 infrared LEDs—850 nm with power of 3.5 mW per LED, 4.45 mW/cm^2^, radiant exposure of 5.35 J/cm^2^, will be used for photobiomodulation. The irradiated area will be 14.13 cm^2^, and energy of 75.6 J, in the TMJ region and in the bilateral masseter and temporal muscles. Participants from all groups will be reassessed after the first therapeutic intervention, and at the end of treatment.

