**Table 1 T1:**
[figure not shown]
Diagnostic subgroups according to RDC/TMD.

Exclusion criteria: present occlusal alterations; use of any type of dental prosthesis; being in orthodontic or physiotherapeutic treatment; necessity of initiating the use of any type of medication during any of the phases of the study.

The randomization will be performed, through the electronic address www.randomization.com, being a 1:1 randomization in blocks, with permutation and change in the size of the blocks. The participants will then be sent for the interventions according to each group, will be evaluated after the first therapeutic intervention, and all will be reevaluated at the end, following the same evaluation sequence used initially (Fig. 2).

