### Visual analog scale

3.3

This scale will be used for pain assessment and consists of a 10 cm line with 0 (no pain) printed on one end and 10 (debilitating pain) printed on the other end. Participants will be asked to mark a spot on the line that represents the intensity of the current pain. The researcher will then use a ruler to record the distance of zero to obtain a numerical representation of the pain level. These procedures will be performed before and after the first session and at the end of treatment.

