### Mandibular range of motion

3.4

The volunteer will be instructed to open his mouth as much as possible. The maximum vertical mandibular movement will be measured (in mm) as the distance between the maxillary and mandibular central incisors determined with the aid of a digital caliper. The volunteer will then be instructed to put pressure on the lower teeth with the mouth open and move the jaw to the right and left to determine the excursion (distance between the upper and lower midpoints). These procedures will be performed before and after treatment. This procedure composes the clinical evaluation of RDC/TMD.

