### Statistical analysis

3.6

The results obtained will be submitted to the Shapiro-Wilk statistical analysis to evaluate the normality. If the data obeys a Gaussian curve, the Analysis of Variance (ANOVA) of repetitive measures will be used with significance level *p* < 0.05. If the data are not parametric, the Kruskal–Wallis test will be used.

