### Interruption of interventions

5.2

The participant will be free to leave the study, at any time, without any kind of loss. If participants become ill or do not adapt to therapy, it will not be possible to continue therapy with LEDs. Interventions will be performed while the participants are in the university, to facilitate their participation and to avoid absences. No adverse effects are expected.

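### In its classical form, the repeated-measures ANOVA in section 3.6 would drop readings already taken from anyone who leaves after session 1; a mixed model would keep them

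*Protocol article*

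**What the plan says.** All of this is in the protocol article.

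- **Test (3.6 Statistical analysis).** After a Shapiro-Wilk check, normal data go to repeated-measures ANOVA: "the Analysis of Variance (ANOVA) of repetitive measures will be used with significance level" p < 0.05. Otherwise, "If the data are not parametric, the Kruskal–Wallis test will be used".
- **Readings.** The Abstract (Methods) states: "Participants from all groups will be reassessed after the first therapeutic intervention, and at the end of treatment". Section 2.4 agrees: participants "will be evaluated after the first therapeutic intervention, and all will be reevaluated at the end, following the same evaluation sequence used initially". For VAS, section 3.3 is explicit: "These procedures will be performed before and after the first session and at the end of treatment". Section 3.4 words range of motion more loosely: "These procedures will be performed before and after treatment". Section 3.5 gives no time points for electromyography.
- **Duration (Abstract, Methods).** Participants are "submitted to 6 non-consecutive sessions of photobiomodulation totaling 2 weeks of treatment".
- **Leaving (5.2 Interruption of interventions).** "The participant will be free to leave the study, at any time, without any kind of loss". The same section says LED therapy cannot go on after illness or failure to adapt to it. It also says sessions take place while participants are at the university, so that fewer are missed.
- **Size (2.3 Sample calculation).** 11 per group, alpha 0.05 (Z = 1.96), power 0.80. The only adjustment mentioned is about 5%, for non-normality.

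The article states no rule for an incomplete set of readings.

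**The concern.** The VAS schedule has an early reading, taken around session 1, and a late one at the end of treatment. Most opportunity to leave falls between the two. Someone who leaves in that interval has given two of three readings, and the second already shows that person's response to the first session.

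Classical repeated-measures ANOVA works on a complete person-by-time table. Someone without the last reading drops out entirely, so the estimates at the earlier time points also become completer estimates. With 11 per group, each person lost is about 9% of an arm (1/11).

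What is at stake is mainly precision: readings collected and paid for would go unused. A secondary worry is that people may leave because of pain, which would make completers unrepresentative.

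**Working it through.** **1. Difference implied by the plan's sample size.** The means and variances behind section 2.3 are in a figure that is not shown, so 11 per group cannot be reproduced forwards. Working backwards with the usual two-sample normal formula, n = 2(1.96 + 0.8416)²/d²:

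- d = 2.8016 × √(2/11) = 1.195 SD gives exactly n = 11.
- Any d below 2.8016 × √(2/10) = 1.253 SD also rounds up to 11.

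I use 1.195.

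**2. Readings lost.** Assume 6 of 33 leave after session 1 (2 per arm).

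- Readings taken: 33 × 3 − 6 = 93.
- Readings from complete cases: 27 × 3 = 81.
- Recorded but unused: 93 − 81 = 12 (6 baseline, 6 post-session-1).

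On an invented data set of this shape, a standard repeated-measures ANOVA routine (time factor only) refused to run because the data were unbalanced. A mixed model with group, time and their interaction used all 93.

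**3. Effect on an illustrative session-1 comparison, LED versus placebo.** The plan does not name this test; it serves as a yardstick. Power is from the noncentral t distribution with noncentrality d√(n/2) and 2n − 2 degrees of freedom, two-sided 0.05. The normal approximation is alongside.

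| n per arm | noncentrality | t-test power | normal approximation |
|---|---|---|---|
| 11 | 2.80 | 0.760 | 0.80 |
| 10 | 2.67 | 0.715 | 0.76 |
| 9 | 2.53 | 0.663 | 0.72 |
| 8 | 2.39 | 0.604 | 0.67 |

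The standard error rises by √(11/10) − 1 = 4.9% with one leaver per arm and √(11/9) − 1 = 10.6% with two. At d = 1.253 the normal-approximation powers are 0.836, 0.800, 0.757 and 0.707. A mixed model keeps 11 versus 11 at session 1.

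**4. Range of losses.** Assumed dropout of 5%, 10% or 20% leaves about 31, 30 or 26 complete cases of 33.

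**5. Bias.** Assumptions: VAS SD 2, true session-1 difference −1.00, log-odds of leaving −2.2 + 0.6 × (VAS after session 1 − 4). Simulated leaving is 11.8% on LED and 18.0% on placebo.

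- Raw post-session-1 difference in completers: −0.879, against −1.00.
- Difference in change from baseline: −0.976, against −0.998, a bias of about 0.02. Re-runs with baseline-to-session-1 correlations of 0.5 to 0.8 give 0.02 to 0.06.
- End-of-treatment difference: −1.44 in completers, −1.51 from the model, about −1.50 true.

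A deliberately extreme case, in which the two worst session-1 scorers leave one arm only (correlation 0.6, true difference 0), shifts the completer change contrast by 0.127 − 0.007 = 0.12 SD. Its sampling standard deviation is about 0.40 SD.

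**The case against.** **The article does not say that anyone is deleted.** A reader might infer that it does. It does not: deletion follows from the classical form of the test, and the analysis can also be run after imputation or fitted as a mixed model. An analysis plan not shown may provide for this, and a missing-data policy is commonly left to such a plan. That stands, so the point is conditional. What remains is that section 3.6 fixes a test whose ordinary form fits this schedule poorly.

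**Kruskal–Wallis would keep the readings.** Run at each time point, it would. The point covers the Gaussian branch only.

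**Three readings are not explicit for every outcome.** Correct. The Abstract and section 2.4 imply three evaluations throughout, but only the VAS section states them. If range of motion is measured only before and after treatment, no session-1 reading of it exists to lose.

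**The plan names no session-1 LED-versus-placebo test and no immediate-effect objective.** Also correct. The power figures are therefore not the power of the planned analysis.

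**Losses may be few.** Treatment lasts two weeks, sessions are on campus, and section 2.4 intends everyone to be reassessed at the end. Someone who stops therapy but attends the last assessment is not lost at all. Two leavers per arm (18%) is an assumption, not a forecast.

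**Bias is slight.** A reader might infer that pain-related leaving would seriously distort the result. The −0.88 against −1.00 is a raw post-session difference, whereas the group-by-time term concerns change, where the bias is about 0.02.

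**Conclusion.** The point holds as a modest improvement in method. For normally distributed outcomes, and most clearly for VAS, the named test in its classical form would leave unused the readings already taken from anyone who withdraws after session 1.

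The cost is precision: about 4 to 5 points of power for the first leaver per arm and about 10 for two (0.760 to 0.663) in an illustrative session-1 comparison. This rests on the 1.195 SD difference implied by the sample size, on assumed numbers of leavers, and on no other handling of missing readings being planned. If nobody leaves, nothing is lost.

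Bias in change from baseline is negligible under graded, pain-related leaving. Only an extreme one-sided pattern produces a visible shift, and that is still well inside sampling error. The documents do not support a claim that the trial's conclusions would be invalid, or that the plan prescribes a completer analysis.

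**What to change.** In section 3.6, replace repeated-measures ANOVA with a likelihood-based linear mixed model with group, time and group-by-time terms and a small-sample degrees-of-freedom correction such as Kenward–Roger. Fit it to all randomised participants in their assigned group, using every available reading, so that nobody is removed for lacking a later one.

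The cost is slightly more analysis work and reliance on a missing-at-random assumption, meaning that leaving depends only on what has been observed. No extra participants, visits or staff are needed, and with complete data the result is essentially that of the planned ANOVA. A sensitivity check that gives leavers no improvement is optional and can be left to the analysis plan.

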### Sample calculation

2.3

To calculate the sample size, data from the paper by Herpich et al^[22]^ was used. Initially we established an error = 

, where 

 are the mean values of groups 1 and 2. Assuming that both samples have the same size (n_1_ = n_2_), the sample size can be obtained using the following relation: where 

 are the variances of groups 1 and 2, respectively. 
[figure not shown]

Assuming also that the studied groups have normal or approximately normal distribution, and that the sample size will be sufficiently large for a level of significance *α* = 0.05 a value of *Z* = 1.96 is obtained. For the sample size calculation it was also established that the power of the test should be 1 – *β* = 0.80. If the normal distribution hypothesis is rejected, the sample size should be corrected by approximately 5%. We obtain the following sample sizes: LED group: 11 participants, Placebo Group: 11 participants, and Control Group: 11 participants.

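### The Kruskal-Wallis fallback in section 3.6 does not test the comparison made by the repeated-measures ANOVA it replaces, so a normality pre-test decides which question is answered

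*Protocol article*

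**What the plan says.** Section 3.6 (Statistical analysis) sets a two-branch rule. First, "The results obtained will be submitted to the Shapiro-Wilk statistical analysis to evaluate the normality". If normality is supported, "the Analysis of Variance (ANOVA) of repetitive measures will be used with significance level" of p < 0.05. If it is not, "If the data are not parametric, the Kruskal–Wallis test will be used". The article does not say which response, visit or baseline handling the second branch uses, and it names no paired or repeated-measures companion test.

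The data are repeated within person. Section 3.3 says of the VAS: "These procedures will be performed before and after the first session and at the end of treatment". The abstract applies the same pattern to everyone: "Participants from all groups will be reassessed after the first therapeutic intervention, and at the end of treatment". Section 2.4 also describes an evaluation after the first intervention and another at the end. Section 3.4 words range of motion more narrowly, "These procedures will be performed before and after treatment", which is still two linked values per person.

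**The concern.** By choosing repeated-measures ANOVA, section 3.6 recognises that each person contributes correlated values and that change over time by group is of interest. The fallback named in the same paragraph has none of these features. It ranks one set of independent values and asks whether the groups differ in location. The two branches are therefore different analyses of different questions, not two versions of one analysis.

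Two things are at stake. The first is interpretation: the hypothesis tested for an outcome is settled by a normality test on the trial's own results, and different outcomes or visits could fall into different branches. The second is efficiency: with 11 people per group, an analysis that leaves out the baseline, or uses it poorly, gives up power that costs nothing to keep.

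**Working it through.** **Inputs from the document.** Three groups: "which will involve 33 individuals (n = 11 per group) of both sexes". Three VAS measurements per person (section 3.3). Two-sided 5% level: "for a level of significance *α* = 0.05 a value of *Z* = 1.96 is obtained" (section 2.3). Planned power 0.80 (section 2.3).

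**Inputs that are assumptions.** The within-person correlation rho is not given; 0.3 to 0.7 is used, equal between all pairs of visits. The effect size is not given in the readable text, so it is back-solved from the stated sample size.

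**The plan's own figure.** The two-sample formula is n = 2(1.96 + 0.8416)² / d². Setting n = 11 gives d = 2.8016 × √(2/11) = 1.195, and putting 1.195 back returns 11 per group and power 0.800. This is circular, so it does not reproduce the plan's calculation. It only supplies an effect consistent with the stated size.

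**What each use of Kruskal-Wallis has to work with.** With SD 1 at each visit, the effect divided by the SD of the analysed quantity is:
- end value: d = 1.195;
- change from baseline: d / √(2(1 − rho));
- end value adjusted for baseline: d / √(1 − rho²).

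| rho | 0.3 | 0.5 | 0.7 |
|---|---|---|---|
| End value | 1.195 | 1.195 | 1.195 |
| Change from baseline | 1.01 | 1.195 | 1.54 |
| Baseline-adjusted | 1.25 | 1.38 | 1.67 |

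The adjusted analysis is ahead in every column.

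**Simulated power.** Set-up: 3 × 11 people, normal data, LED shifted by 1.195 SD at the end and by half of that after session 1, three-group test at 5%, 2,500 runs per setting.

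| rho | 0.3 | 0.5 | 0.7 |
|---|---|---|---|
| Kruskal-Wallis, end value | 76% | 75% | 76% |
| Kruskal-Wallis, change | 60% | 76% | 94% |
| Rank ANCOVA | 79% | 85% | 95% |
| ANCOVA | 82% | 89% | 97% |

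A separate run over the same range of rho and the same effect gave 75-77%, 62-94%, 80-96% and 83-97%. These agree to within about two points and are the figures used in the conclusion. With log-normal data (4,000 runs) the values at rho 0.3 / 0.5 / 0.7 were 74 / 76 / 74% for the end value, 39 / 54 / 76% for change and 78 / 86 / 94% for rank ANCOVA.

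**Type I error, one value per person.** In the log-normal simulation (8,000 null runs, rho 0 to 0.8) it was 0.043-0.049 for the end value, 0.040-0.050 for change and 0.044-0.052 for rank ANCOVA. All three hold the nominal level.

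**Type I error if visits were pooled.** Treating three correlated values as three people inflates the between-group variance by about 1 + 2·rho. For three groups the reference distribution is chi-square with 2 df, so the rejection rate is roughly 0.05^(1/(1 + 2·rho)):
- rho 0.3: 0.05^(1/1.6) = 0.154;
- rho 0.5: 0.05^(1/2.0) = 0.224;
- rho 0.7: 0.05^(1/2.4) = 0.287.

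Simulation gave 0.147, 0.216 and 0.295. Pooling only the two post-baseline values gave 0.094, 0.131 and 0.170.

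**How often the gate might trip.** For an assumed VAS clipped at 0 with SD 2, Shapiro-Wilk rejected as follows:

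| Assumed mean | n = 11 | n = 33 |
|---|---|---|
| 1 | 53-56% | 99% |
| 2 | 17% | 65% |
| 3 | 5-6% | 12-13% |

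At means of 4 to 5 it was about 3-5%.

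**The case against.** The strongest reply is that a condensed article need not spell out the response variable and visit for a named test, and that a sensible analyst would run Kruskal-Wallis on change from baseline. That use is ordinary, draws on the baseline and holds the 5% level. At a correlation of 0.7 with normal data it comes close to ANCOVA (94% against 97%). This stands. A reader might infer that the fallback cannot use the baseline at all, and that would be wrong.

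A reader might also infer that the trial faces a 15-29% false-positive rate. The article does not support this: it nowhere says that visits will be pooled as independent observations. Nor does it exclude pooling, so the figure is conditional.

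A third tempting inference is that the main outcome will probably go down the fallback route. The article names no main outcome, gives no VAS mean or SD, and says only that pain should be reduced with LED, not that scores will approach zero. Floor effects are also argued for the VAS alone, not for caliper or EMG data.

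Finally, much of the power gap comes from baseline adjustment and not from ranking. In the same kind of normal-data simulation, with an effect of 1.2 SD, one-way ANOVA on the end value had 79-80% power against 76-77% for Kruskal-Wallis, so ranks alone cost about 3-4 points. The ANCOVA and rank ANCOVA compared here also leave out the middle visit, so their gain comes from the baseline alone. Nothing here shows the repeated-measures ANOVA itself to be wrong, and its power was not computed.

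What the reply does not remove is the mismatch on the page. The article chose a specific substitute test, and that test does not fit the repeated-measures design which its own first branch recognises.

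**Conclusion.** The point holds as a mismatch between test and design. If Shapiro-Wilk rejects, the plan moves to a test with no time, group-by-time or covariate term, so the question answered depends on a pre-test of the outcome data. The article does not say whether raw values, changes or residuals are to be tested.

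On either valid single-value use the 5% level is kept and power is lost: 75-77% for the end value and 62-94% for change, against 80-96% for rank ANCOVA and 83-97% for ANCOVA. This rests on an assumed correlation of 0.3-0.7 and a back-solved effect of 1.195 SD. These are three-group tests, while the planned 80% comes from a two-group formula, so the distance from 80% should not be put down to the fallback alone.

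Type I error of about 15-29% would follow only from pooling all three visits. The fallback would be used often for the VAS only if scores lie near zero, which the document does not allow one to judge. Severity: should fix.

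**What to change.** In section 3.6, remove the Shapiro-Wilk gate and the Kruskal-Wallis branch. Pre-specify one between-group analysis per outcome, adjusted for its baseline value, with the visit and contrast stated. Check the residuals of that model. If they are clearly non-normal, keep the same baseline-adjusted contrast and obtain its p-value by rank ANCOVA or by permuting group labels. The residual check then changes only how the contrast is tested, not which comparison is made.

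The cost is one rewritten paragraph and slightly more programming, with no extra patients or visits. The downside is that a rank-based result, if used, is harder to express in VAS units.

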## Discussion

4

Photobiomodulation, that is, the use of several light sources, sometimes in the same device, can be used as a therapeutic resource.^[33]^ A study of the histological analysis of rats showed positive results in the reduction of the carrageenan—induced inflammatory reaction in the TMJ after the use of the infrared LED—850 nm (100 mW, 10 J) and compared with the group using laser—780 nm (70 mW, 10 J). The criteria of histological evaluation were the percentage of neutrophils and lymphocytes in relation to the total of cells in the observed area, and the percentage of blood vessels in relation to the observed area.^[34]^ Prior to this, a study investigated the effects of phototherapy with the combination of different light sources on the nonspecific pain of a larger joint: the knee. The combination of 905 nm super-pulse laser and 875 and 640 nm LEDs were used, which proved effective in reducing pain and improving quality of life in patients with knee pain.^[35]^

The use of photobiomodulation with infrared LEDs 880 nm ± 20, energy density 4 J/cm^2^, presented results, after electromyographic evaluation, which pointed to the increase in electrical activity and muscle recruitment, this suggested the optimization of muscular activity with the use of therapy with LED, without causing side effects, such as elevation of strength and increase of blood lactate levels.^[27]^ Infrared LED phototherapy of 950 nm, but with different energy density and power, 3.2 J/cm^2^, 160 mW, had previously been used in skeletal muscles. The study did not present significant results when investigating its analgesic effect in pain induced experimentally in flexor muscles of the elbow of humans.^[36]^

Decreased pain and increased mandibular mobility in patients with TMD were also found after the use of LED photobiomodulation when applied to the masticatory muscles and points around TMJ. These results were achieved both with the use of 880 nm infrared LEDs, energy density of 7 J/cm^2^, and power of 0.03 W^[37]^; with 850 ± 10 nm, energy density 18 J/cm^2^, and power of 150 mW; as well as the use of red LED 630 ± 10 nm, 18 J/cm^2^, and power of 150 mW.^[23]^ The decrease in pain intensity in masticatory muscles was found even after single application, combining super-pulse laser 905 nm, 0.9 mW; Red LED—640 nm, 15 mW; infrared LEDs—875 nm, 15 mW, at different radiation doses: doses of 2.62 J/dot, 5.24 J/spot, and 7.86 J/spot in women with TMD.^[22]^

The effectiveness of photobiomodulation as in the treatment of TMD has been proven by several authors,^[17,22,37,38]^ but there are few controlled clinical studies analyzing the performance of photobiomodulation with different LED wavelengths in the same device with several simultaneous irradiation points in patients with TMD.

